**Methods:**

This is a pilot, prospective, randomized, repeated-measures, single-blind study design. We expect to enroll 28 participants randomly assigned to one of two treatment arms: arm 1 (tACS/CBTp, n=14) or arm 2 (sham tACS/CBTp, n=14; tACS is sham, but CBTp is active). The intervention with active or sham tACS/CBTp will take place weekly for 16 weeks. Primary outcome measures—electroencephalogram, Positive and Negative Syndrome Scale, 16-item Negative Symptom Assessment, and Cognitive Flexibility Scale—will evaluate the efficacy of treatment at the end of the intervention and at the two follow-ups. We will use SPSS (version 29, IBM Corp); the main tests will include repeated measures and mixed design ANOVA.

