## Methods

### Trial Design

#### Description

This is a prospective, randomized, repeated-measures, single-blind study design. Preintervention, eligible participants will be randomly assigned to one of two treatment arms: arm 1 (tACS/CBTp, n=14) or arm 2 (sham tACS/CBTp, n=14; tACS is sham, but CBTp is active). In the intervention (16 weeks), participants in arms 1 and 2 will receive once-weekly tACS/CBTp or sham tACS/CBTp. Individuals with schizophrenia (*DSM-5* [*Diagnostic and Statistical Manual for Mental Disorders* {Fifth Edition} criteria) stratified by age and sex. The investigators expect 150 potentially eligible patients from Providence Care Mental Health Services, with 33-40 participants consenting to participate and 28 participants undergoing the research activities (see Figure 1).

Participants will be randomized 1:1 to one of two arms and stratified by age (18-30, 31-55, and >60 years) and by sex (male or female).

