### Enrollment and Randomization

After the screening visit, participants will be randomized in a 1:1 ratio with stratification according to age and sex.

Maintaining the blind is covered by the device, which induces a discrete tickling sensation at the starting point of the intervention for participants on sham tACS. This study is single blind, being blinded only for participants. In case of emergency, the research team would be aware of the interventional (or sham) nature of the problem. Communication with participants regarding this aspect will be possible only at the end of the study, at the end of visit 6 (second follow-up), at the patient’s request, or after they withdraw from the study. At the study closure, each participant will receive a debriefing letter containing unblinding disclosure.

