### Statistical Considerations: Sample Size

This is a pilot randomized study with 28 participants (14 per arm). The primary goals are to evaluate recruitment feasibility, acceptability, and safety, and to produce unbiased estimates of the standard deviation and preliminary effect sizes of the primary outcome to inform sample-size calculation for a future definitive trial [31]. A target of 28 participants is consistent with common pilot rules-of-thumb (approximately 12-20 per arm) and provides sufficient precision to estimate recruitment and retention rates and the outcome variance. This pilot is not powered for hypothesis testing of efficacy (with n=14 per group, the minimal detectable standardized effect is large, ~*d*=1.1); outcome analyses will therefore be descriptive and will report effect estimates with 95% CIs as inputs for future sample-size calculations. To allow for expected attrition (approximately 15%-20%), we will recruit up to 33-40 participants. The generalizability of our findings is limited by the small sample size (n=28) and recruitment from a single treatment site. Patients in this cohort may differ from the broader schizophrenia population with respect to illness chronicity, symptom severity, comorbid psychiatric or medical conditions, and sociodemographic characteristics. In addition, the specialized treatment context may not reflect the experiences of individuals receiving care in community or primary care settings, where clinical resources and treatment approaches may vary. These factors restrict the extent to which the present results can be applied to other patient populations. Replication in larger, multisite, and more heterogeneous cohorts will be essential to establish the robustness and external validity of the findings.

The statistical analysis plan will use SPSS (version 29, IBM Corp) for the main tests, including effect size (Cohen *d*) and a 95% CI: repeated measures, mixed design analysis of variance, and *t* tests for two-group comparisons. Sex and gender differences will be examined using regression models that include biological sex, BSRI masculinity and femininity scores, and their interaction terms, with exploratory subgroup analyses based on BSRI classifications.

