### Potential Clinical Benefit

A total of 28 clients will have the opportunity to benefit from our CBTp intervention with or without tACS.

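### The recruitment ceiling of 40 does not follow from 15%-20% attrition, and 28 serves both as the number randomised and as the number left after attrition

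*Protocol article*

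**What the plan says.** The protocol article gives the number 28 in several places, at different stages of participant flow.

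- **Statistical Considerations: Sample Size.** The total is 28, or 14 per arm. The sensitivity statement is tied to that number: "with n=14 per group, the minimal detectable standardized effect is large", given as d of about 1.1. The target of 28 is supported by a rule of thumb of roughly 12-20 per arm. The recruitment target follows: "To allow for expected attrition (approximately 15%-20%), we will recruit up to 33-40 participants". The section adds that the pilot is not powered for efficacy and that outcome analyses will be descriptive.
- **Abstract, Methods.** "We expect to enroll 28 participants randomly assigned to one of two treatment arms", with 14 in each.
- **Trial Design, Description.** Arms of 14 at assignment, and a flow "with 33-40 participants consenting to participate and 28 participants undergoing the research activities".
- **Potential Clinical Benefit.** "A total of 28 clients will have the opportunity to benefit from our CBTp intervention with or without tACS".
- **Monitoring Plan.** The 25% source-verification sample is computed as 7 of 28.
- **Enrollment and Randomization.** "After the screening visit, participants will be randomized in a 1:1 ratio with stratification according to age and sex". In Table 2, consent is part of that screening visit.
- **Abstract, Results.** Of 15 people described as enrolled, two were screening failures and one withdrew after the second intervention.

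**The concern.** There are two separate difficulties.

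First, the sample-size section gives attrition as the only reason for recruiting 33-40, but the stated attrition rate does not produce the upper end of that range.

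Second, the section's own logic is that more than 28 are recruited so that 28 remain. The abstract, the trial design description and the clinical-benefit statement instead have 28 entering treatment, and the design description places the 33-40 at consent. On those statements the margin between 33-40 and 28 is used up before randomisation, and nothing covers dropout over the 29 weeks of participation.

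This affects the pilot's own aims. They include estimating the outcome SD, preliminary effect sizes, and recruitment and retention rates. The number analysed sets the precision of the first two. The number randomised is the natural denominator for retention, and the article leaves it at either 28 or 33-40. Recruitment is under way, so the team also needs to know when to stop randomising.

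**Working it through.** **Inputs from the article:** 28 in total, 14 per arm, 1:1 allocation; attrition 15%-20%; recruitment 33-40; d about 1.1 at 14 per group.

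**Assumptions (not stated in the article):** two-sided 5% test, 80% power, two-sample t test with equal arms.

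**1. The plan's detectable effect.** Solving the noncentral t for 80% power at n = 14 per group gives d = 1.10. The normal approximation, (1.96 + 0.84) × √(2/14), gives 1.06. The stated value of about 1.1 is reproduced.

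**2. The recruitment range.** Number to recruit = 28 / (1 − loss).
- 15% loss: 28 / 0.85 = 32.9, so 33. The lower end is reproduced.
- 20% loss: 28 / 0.80 = 35. The upper end of 40 is not reproduced.
- Loss implied by 40: 1 − 28/40 = 30%.

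**3. If 28 are randomised and 15%-20% then leave.**
- 28 × 0.85 = 23.8 and 28 × 0.80 = 22.4, so about 22-24 are analysed, or 11-12 per arm.
- Detectable d: 1.20 at 12 per arm, 1.26 at 11 per arm.
- Power at d = 1.1: about 73% at 12 per arm and 69% at 11, against 80% at 14.
- 95% CI half-width for the mean difference in SD units, t(0.975; 2n − 2) × √(2/n):
  - n = 14: 2.056 × 0.378 = 0.78
  - n = 12: 2.074 × 0.408 = 0.85
  - n = 11: 2.086 × 0.426 = 0.89

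**4. If 33-40 are randomised and the same 15%-20% leave.**
- From 33: 33 × 0.85 = 28.1 and 33 × 0.80 = 26.4.
- From 40: 40 × 0.85 = 34 and 40 × 0.80 = 32.
- About 13-17 per arm remain. Detectable d is about 1.15 at 13 per arm and 0.99 at 17 per arm.

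| Randomised | Analysed per arm after 15%-20% loss | Detectable d |
|---|---|---|
| 28 | 11-12 | 1.26-1.20 |
| 33-40 | 13-17 | 1.15-0.99 |
| 14 per group analysed, as stated | 14 | 1.10 |

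**The case against.** The strongest reply is that little is wrong and nothing depends on it. Several parts of that reply stand.

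- The lower end of 33 matches 15% loss, and the required 33-35 lies wholly inside 33-40. The text also says *up to*, which is a ceiling. The fault is an over-wide upper end, not a shortfall.
- The d of about 1.1 is correct for 14 per group and is stated conditionally on that number. It serves only to show that the pilot cannot test efficacy. A value of 1.20-1.26 would reinforce that message.
- The 22-24 figure is a scenario. If the 15%-20% is meant to cover loss between consent and randomisation, the article gives no rate for loss afterwards. The progress report counts screening failures among the enrolled, so the stage is open.
- The rule of thumb of 12-20 per arm is approximate, and the article does not say that it counts analysed participants. Falling to 11 per arm is at most a marginal breach.
- Screening failure could explain 40. With the reported 2 of 15 failing, 28 / (0.80 × 13/15) is about 40. The article, however, attributes the range to attrition alone.

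A reader might infer that the stated 14 per group will not be reached. The document does not support that as a fact. It holds only if 28 are randomised and the full 15%-20% is lost afterwards. If 33-40 are randomised, as the sample-size section read alone allows, 14 per group is met or missed by about one per arm.

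The reply does not remove the unsupported 40, or the use of one number at two stages.

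**Conclusion.** The point holds in a limited form. The upper recruitment figure of 40 does not follow from 15%-20% attrition, which gives 33-35; 40 implies 30%. The number 28 is what remains after attrition in the sample-size section, but the number randomised or treated in the abstract, the trial design description and the clinical-benefit statement. Under those latter statements no allowance is left for loss after randomisation.

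If that reading is the intended one and the stated attrition falls after randomisation, the analysed number is 22-24. The detectable d rises from 1.10 to about 1.20-1.26, and the CI half-width from 0.78 to about 0.85-0.89 SD. These values rest on the assumed two-sided 5% level and 80% power, which do reproduce the article's 1.1. If 33-40 are randomised, the stated 14 per group is broadly secure.

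The consequence is modest, since the trial is a descriptive pilot and no efficacy claim hangs on d. It still deserves correction, because precision and retention are among the pilot's stated purposes.

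**What to change.** State once whether 28 is the number randomised or the number completing, and at which stage the 15%-20% applies.

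- **If 28 is randomised:** give the expected analysed number as 22-24, assuming the 15%-20% is loss after randomisation, and restate the detectable d (about 1.20-1.26) and the expected precision, with the significance level and power they assume. No further participants are needed.
- **If 28 is completing:** give the randomised target as 33-35 (34-36 with equal arms) and align the abstract, the trial design description, the 7-of-28 verification sample in the monitoring plan, and the clinical-benefit statement.
- **In either case:** drop 40, or name the further loss it covers, such as screening failure, with its assumed rate.

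The first option costs only wording and a slightly less favourable stated figure. The second also commits the team to randomising 5-7 more than 28 (33 − 28 and 35 − 28), or 6-8 more with equal arms. That is within the recruitment range already announced.

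### The named mixed-design ANOVA and t tests use incomplete visits, baseline and strata poorly in a pilot expecting 15–20% attrition; whether 28 are randomised or analysed is also unsettled

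*Protocol article*

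**What the plan says.** The analysis paragraph of Statistical Considerations: Sample Size lists the main tests as "repeated measures, mixed design analysis of variance", with t tests for two-group comparisons, Cohen d and 95% CIs, all in SPSS. The abstract names the same ANOVA methods. No baseline covariate or stratification term is named for the arm comparison. Sex enters only a separate regression on sex and gender differences, although randomisation is stratified by sex and age (Trial Design; Enrollment and Randomization). Mixed models appear once, under Primary Outcome Measures, as an alternative to t tests for the between-group EEG comparison.

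Table 2 schedules PANSS and NSA-16 at four visits, CFS at five and EEG at two.

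On numbers, the sample-size section states "This is a pilot randomized study with 28 participants (14 per arm") and that with 14 per group "the minimal detectable standardized effect is large, ~*d*=1.1". It then adds "To allow for expected attrition (approximately 15%-20%), we will recruit up to 33-40 participants". The abstract says "We expect to enroll 28 participants randomly assigned to one of two treatment arms". The trial design section expects "33-40 participants consenting to participate and 28 participants undergoing the research activities".

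**The concern.** The deliverable of this pilot is an effect estimate with its interval: the plan "will report effect estimates with 95% CIs as inputs for future sample-size calculations". The analysis should therefore use all the randomised data and the collected baseline.

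A classical mixed-design ANOVA over all visits removes a participant's whole record on a scale if one visit is missing. The losses are unlikely to be random. Criteria for Withdrawal lists a condition that worsens or fails to improve, and suicidal ideation with a plan, among the reasons for leaving. Estimates from complete records alone are open to bias. A likelihood-based mixed model keeps every observed visit and relies only on missingness being explained by the observed data.

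Precision is also lost. A t test on end-of-treatment scores ignores the baseline value. The ANOVA brings baseline in as one more repeated measurement, which is less efficient than adjusting for it.

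Finally, the detectable effect depends on how many people are analysed, and the sections do not agree on whether 28 is the number before or after attrition.

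**Working it through.** **Inputs from the protocol.** 14 per arm; d about 1.1; attrition 15–20%; recruitment up to 33–40; visits per scale from Table 2.

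**Assumptions.** Two-sided alpha 0.05 (consistent with the 95% CIs), 80% power (not stated, but it reproduces the plan's figure), and baseline–outcome correlation r = 0.3, 0.5 or 0.7 (not given).

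**1. The plan's own figure.** Two-sample t test, noncentral t with noncentrality d/√(1/n1 + 1/n2) and n1 + n2 − 2 degrees of freedom. At 14 v 14 the detectable d is 1.100, so the stated 1.1 reproduces. The 95% CI half-width is t(0.975, 26) × √(2/14) = 0.78 SD.

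**2. Baseline adjustment at 14 per arm.** ANCOVA multiplies the residual SD by √(1 − r²) and costs one degree of freedom, which moves 1.100 to about 1.102 before scaling. A change score multiplies the SD by √(2(1 − r)), taking equal variances at the two times.

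| r | √(1 − r²) | ANCOVA d | Change-score d | Unadjusted t test d |
|---|---|---|---|---|
| 0.3 | 0.954 | 1.05 | 1.30 | 1.10 |
| 0.5 | 0.866 | 0.95 | 1.10 | 1.10 |
| 0.7 | 0.714 | 0.79 | 0.85 | 1.10 |

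ANCOVA does better than both alternatives at each r. The gain over the unadjusted test is small at r = 0.3 and large at r = 0.7; the gain over the change score runs the other way. Any further gain from adjusting for sex and age cannot be computed from the document.

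**3. If 28 are randomised.** 28 × 0.85 = 23.8 and 28 × 0.80 = 22.4, so about 12 or 11 per arm.

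| Analysed per arm | Detectable d, unadjusted | Power at d = 1.1 | 95% CI half-width (SD) | ANCOVA d at r = 0.3 / 0.5 / 0.7 |
|---|---|---|---|---|
| 14 | 1.10 | 0.80 | 0.78 | 1.05 / 0.95 / 0.79 |
| 12 | 1.20 | 0.73 | 0.85 | 1.14 / 1.04 / 0.86 |
| 11 | 1.26 | 0.69 | 0.89 | 1.20 / 1.09 / 0.90 |

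**4. If 28 are to be analysed.** 28/0.85 = 32.9, so 33; 28/0.80 = 35. Both lie inside 33–40. If 33–40 are all randomised, completers range from 33 × 0.80 = 26.4 to 40 × 0.85 = 34, and the detectable d from about 1.15 (13 per arm) to 0.99 (17 per arm). The top of the range, 40, would correspond to a loss of 1 − 28/40 = 30%, above the stated 15–20%.

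**The case against.** The strongest reply is that this is a pilot. The section says "This pilot is not powered for hypothesis testing of efficacy", calls the outcome analyses descriptive, and offers d of about 1.1 as a caveat, so moving it to 1.2 changes no decision. That stands as far as power goes. It does not remove the point about bias and interval width, because the effect estimate with its interval is what the pilot is meant to supply.

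A second reply is that missing-data handling and covariates may sit in an analysis plan that is not shown, and that no SPSS procedure or complete-case rule is written down. That is fair for details. But the article itself fixes the main tests, and the listwise behaviour follows from classical mixed-design ANOVA.

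Three stronger readings are tempting, and the document does not support them:

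- A reader might infer that d of about 1.1 cannot be reached under 15–20% attrition. The recruitment allowance in the same section covers it if the extra participants are randomised.
- A reader might infer that anyone with a missed visit is dropped everywhere. A t test at one visit loses only those missing that visit, EEG has two time points, and mixed models are allowed for it.
- A reader might infer that baseline is ignored altogether. The ANOVA uses it through group-by-time; only the t tests as named do not.

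Nor is the figure of 40 an error in itself. It is an upper limit on people consenting or recruited, and the abstract's Results count two screening failures among 15 enrolled, so some of the 33–40 may never be randomised.

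**Conclusion.** The point holds as a choice of method that should be improved. For PANSS, NSA-16 and CFS, the named ANOVA discards partial records and uses baseline inefficiently, and the t tests as named omit baseline and strata. At 14 per arm, baseline adjustment brings the detectable d to about 1.05, 0.95 or 0.79, against 1.10 for the unadjusted t test and 1.30, 1.10 or 0.85 for a change score. These figures rest on the assumed r of 0.3, 0.5 or 0.7, two-sided 5% and 80% power. The size of any bias from complete-record analysis cannot be computed from the document.

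The question of numbers is separate and conditional. The shortfall to about 1.20–1.26 applies only if 28 is the number randomised, which is how the abstract and trial design section read. If 28 is the number analysed, about 1.1 stands. The sections need to be brought into line.

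**What to change.** - **PANSS, NSA-16 and CFS.** Make the primary estimate a likelihood-based repeated-measures mixed model (SPSS MIXED, Satterthwaite or Kenward-Roger degrees of freedom). Include every randomised participant with any post-baseline value. Terms: arm, visit, arm by visit, baseline, sex and age. Enter age as continuous, because the bands in the trial design section (18–30, 31–55, over 60) leave out ages 56–60. Report the week 17 arm difference with its 95% CI.
- **EEG.** Use ANCOVA of the end-of-intervention gamma measure on its baseline value.
- **Numbers.** State whether 28 is randomised or analysed, and align the abstract, trial design and sample-size sections. If randomised, restate the detectable d as about 1.20–1.26 after 15–20% loss for the unadjusted comparison. If analysed, state that 33–35 will be randomised and keep about 1.1.

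The cost is wording, analysis code and a few degrees of freedom for covariates. The software and data collection do not change, and recruitment was still under way at the abstract's reporting date, so the change can be made before analysis.

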**Objective:**

This study aims to elicit cognitive readiness and therapeutic engagement by adding tACS to each CBTp session in individuals with schizophrenia taking their usual medication, to evaluate the possible improvement of the level of functioning, and to determine if the response to intervention is gender specific.

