### Objectives

This study compares the effects of a harmless, low-voltage electrical stimulation (tACS) with placebo stimulation (sham tACS) applied for 20 minutes at the beginning of the CBTp session to increase the efficacy of psychotherapy in people living with schizophrenia.

Primary objectives are to determine whether (1) the new intervention protocol using tACS will enhance the EEG activity, expecting that CBTp will enhance EEG activity in clients with schizophrenia at the end of therapy for both groups, with a better outcome for the group with active tACS stimulation; and (2) tACS applied at the beginning of the CBTp sessions in people with schizophrenia will predict better responses to therapy (compared with the sham tACS/CBTp). CBTp is expected to improve the scores of the PANSS, NSA-16, and Cognitive Flexibility Scale (CFS).

The secondary objectives are to determine whether (1) there will be an improvement of level of functioning and quality of life in both intervention groups, with a superior outcome for the group receiving tACS intervention (psychological and psychosocial tests); (2) higher in-session HRV predicts a better response to CBTp (the expectation is that baseline HRV will predict symptom improvement and increase over the course of therapy); and (3) the response to tACS/CBTp intervention is gender specific; considering that cognitive and emotional status is gender dependent, we expect that the therapeutic response could be gender specific.

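### The sex/gender regression as described names no treatment arm and no arm interaction, so it cannot address secondary objective 3, whether response to tACS/CBTp is gender specific

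*Protocol article*

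**What the plan says.** The Abstract gives as one aim of the study "to determine if the response to intervention is gender specific". The Objectives section lists it as the third secondary objective, to determine whether "the response to tACS/CBTp intervention is gender specific". The Discussion repeats the expectation.

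The analysis is in the last paragraph of Statistical Considerations: Sample Size. The main tests are "repeated measures, mixed design analysis of variance, and *t* tests for two-group comparisons". For sex and gender it states: "Sex and gender differences will be examined using regression models that include biological sex, BSRI masculinity and femininity scores, and their interaction terms". The same sentence then adds subgroups by BSRI class, which it labels exploratory. No other sex/gender analysis appears in the article.

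Three design facts bear on this. CBTp is given in both arms and only tACS is randomized (Trial Design; Table 1). Sex is a stratification factor in the 1:1 randomization. The BSRI is completed at screening, before treatment starts.

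**The concern.** Both arms receive CBTp, so the randomized comparison isolates the addition of tACS. Whether the response to tACS/CBTp is gender specific is therefore a question about effect modification: does the active-versus-sham difference vary with sex or with the BSRI scores? That quantity is an arm-by-sex or arm-by-BSRI interaction.

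The article names sex, two BSRI scores and the interactions among them. Grammatically, the possessive before the interaction terms refers back to those three variables. A model with only these terms estimates an association between sex or gender role and outcome, averaged over arms. That is prognostic information. It contains no treatment comparison, so no sample size would make it answer objective 3.

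The article says effect estimates from this pilot are meant to inform a later trial. A descriptive estimate still has to be an estimate of the right quantity.

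**Working it through.** **1. The plan's own figure.** The same section states that "with n=14 per group, the minimal detectable standardized effect is large", about d = 1.1. Alpha and power are not given. Assuming a two-sided 5% level, 80% power and a two-sample t test (noncentral t, 14 per arm), the detectable effect is d = 1.100. The figure reproduces and is not in dispute.

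**2. Objective and model set against each other.**

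| Needed for objective 3 | Named in the article |
|---|---|
| Arm | No |
| Sex, BSRI masculinity, BSRI femininity | Yes |
| Arm × sex, arm × BSRI scores | No |
| Interactions among sex and BSRI scores | Yes, but not needed for objective 3 |

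The mixed ANOVA and t tests are not said to carry sex or gender as a factor. The BSRI subgroup analyses name no arm contrast, and separate results within subgroups would not test a difference between them.

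**3. What the sex coefficient measures without arm.** With sex balanced across arms, it is the average of the two within-arm sex differences (women minus men). The target is the difference between them. Take three sets of true values, in SD units:

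| Scenario | Sex difference, sham | Sex difference, active | Average | Arm × sex interaction |
|---|---|---|---|---|
| A: same sex difference in both arms | 0.5 | 0.5 | (0.5 + 0.5)/2 = 0.5 | 0.5 − 0.5 = 0 |
| B: sex difference under active only | 0 | 1.0 | (0 + 1.0)/2 = 0.5 | 1.0 − 0 = 1.0 |
| C: opposite directions | −1.0 | 1.0 | (−1.0 + 1.0)/2 = 0 | 1.0 − (−1.0) = 2.0 |

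A least-squares simulation (28 participants, 7 per arm-by-sex cell, outcome SD 1, 2,000 replicates) fitted sex, both BSRI scores and their two-way interactions. The mean sex coefficient was 0.48 in A, 0.48 in B and 0.00 in C. A model with arm, sex and arm × sex gave mean interaction estimates of 0.01, 1.02 and 2.00. The named terms do not distinguish A from B, and in C they miss the interaction altogether.

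**4. Precision of the arm × sex contrast.** No sex split is given, so the cell sizes are assumptions. For an unadjusted difference in differences with m of one sex and 14 − m of the other in each arm:

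SE = √(2/m + 2/(14 − m)) SD; 95% half-width = t(0.975, 24 df) × SE, with t about 2.06.

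| Split per arm | SE (SD) | Half-width (SD) |
|---|---|---|
| 7/7 | √(4/7) = 0.756 | 1.56 |
| 9/5 | 0.789 | 1.63 |
| 10/4 | 0.837 | 1.73 |
| 11/3 | 0.921 | 1.90 |

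At 7/7, the interaction detectable with 80% power (two-sided 5%, noncentral t) is about 2.21 SD, roughly twice the 1.1 for the main comparison.

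**The case against.** The strongest reply is that the sentence is a summary. It says the models include certain terms, which is not an exhaustive list. It also leaves out the outcome, baseline and time, and a separate analysis plan may add arm. That stands to this extent: a reader might infer that the trial will never estimate the right quantity, and the article does not establish that. It does not dispose of the point. The article chose to name the model's terms and its interactions, and the interaction its own objective requires is not among them.

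A second reply is that response might mean improvement in either arm. The Conclusions of the Abstract speak more loosely of therapeutic response. This reading is possible but weaker, because tACS/CBTp is the label of the active arm. Even on that reading, a pooled association could not be attributed to tACS.

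Third, a reader might infer that a significant sex coefficient will be reported as gender-specific response, or that BSRI subgroups will yield chance findings presented as results. Nothing in the article says so. It declares the outcome analyses descriptive and the subgroups exploratory.

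Fourth, a reader might conclude that the sex × BSRI terms and the BSRI subgroups should be dropped. That would be a preference. The article sets out a Gender-Based Analysis Plus aim using the BSRI, and describing how sex and gender role jointly relate to outcome is a legitimate exploratory question.

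**Conclusion.** The point holds as a mismatch between a stated objective and the model described for it. As written, the regression estimates sex and gender-role associations pooled over arms and cannot address secondary objective 3. No number in the plan is wrong.

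Severity is minor to moderate. The objective is secondary, and the pilot's primary goals are feasibility, acceptability, safety and variance estimation. Even the correct interaction would be known only to about ±1.6 SD at best.

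That figure rests on an even sex split, 28 analysed participants and no covariate adjustment. It should not be carried over to a baseline-adjusted model or to interactions with the continuous BSRI scores. The simulation rests on balanced cells. It illustrates which quantity is estimated and does not predict this trial's results.

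**What to change.** State that, for objective 3, each model includes arm, the pre-intervention value of the outcome, one modifier and the arm × modifier interaction. Fit it for sex, then BSRI masculinity, then BSRI femininity, and report each interaction as an exploratory estimate with its 95% CI.

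One modifier at a time means 4 coefficients plus an intercept, leaving 28 − 5 = 23 residual degrees of freedom. Entering all three modifiers and their arm interactions together would need 8 coefficients plus an intercept, leaving 28 − 9 = 19, which is heavy for this sample.

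The sex × BSRI terms and the BSRI subgroups may stay as exploratory description, with a sentence that they are not evidence of a gender-specific response to tACS.

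The cost is wording only. Sex is already a stratification factor and the BSRI is already collected at screening. The downside is that the intervals will be very wide, so the results can only be descriptive, and the text should say so.
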